### 2.3 Procedures

Each participant will take part in two phases of the experiment including familiarization and data collection.

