#### 2.3.1 Familiarization

In the first phase, all subjects will undergo a familiarization session, about 1–2 h before data collection. The study objectives and procedures will be explained to participants and informed consent will be taken from each participant before the study. In the second phase, participants will complete a questionnaire that includes personal and baseline characteristics. Body mass will be measured using a calibrated digital scale, and height will be measured using a single stadiometer. The weight plates used in the trunk muscles fatigue protocol for each participant will be chosen during the familiarization phase. The heaviest weight that participants can perform each exercise 20 times in 40 s in the correct form will be used (Askari and Esmaeili, 2021). During this phase, subjects will be asked to eat their normal meal while avoiding strenuous exercise and performance-enhancing energy drinks for the 48 h prior to data collection sessions (Armstrong et al., 2018).

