#### 2.3.3 Fatigue protocol

The modified Abt protocol will be used in order to induce fatigue of trunk muscles (Abt et al., 2007). The protocol lasts 32 min and consists of four consecutive cycles of eight exercises. Each set consists of exercises in the following order:1) trunk rotation with a medicine ball in a sitting position, 2) prone static torso extension with a medicine ball, 3) lower torso rotation with a medicine ball in a supine position, 4) sit-ups on the incline bench with a weight plate, 5) lateral side binding with a weight plate, 6) lumbar extension rotation with weighted plate, 7) trunk rotation with weighted pulley resistance in standing position, and 8) supine isometric bridge hold. The selection of weight plates for each subject will be performed on a separate day before testing. The heaviest weight with which subjects can perform each exercise 20 times in 40 s in the correct form will be used. Prior to trunk muscle fatigue protocol, a 10- minutes warm-up will be performed including 5 min of *insitu* warming, and 5 min of aerobic stretching, with an emphasis on the hamstring and trunk muscles. Then fatigue protocol will be started. Subjects will perform 20 repetitions of each exercise in 40 s (each repetition in 2 seconds). A pause of 20 s will be between each exercise. The fatigue protocol will be terminated in two ways: 1) when subjects will be no longer able to continue the fourth set of exercises (the last set) with the correct form, and 2) when the subjects will be unable to perform each repetition in 2 seconds in the last set exercises. To ensure occurrence of fatigue, subjects will be rated on their perceived exertion at the end of each phase of the protocol using the 15-point Borg scale (rank 6–20) (Borg, 1970). The point of six represents the absence of fatigue and point of 17–20 indicates failure to perform exercises. If the subjects in the end of fourth round report number 17 or higher, it means the end of the fatigue protocol. If they will report fewer points, they should perform another round until they report the point 17 (Askari and Esmaeili, 2021).

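### Sections 2.3.1 and 2.3.3 give conflicting times for load selection; on the 2.3.1 timing the 48 h exercise restriction comes too late for session 1 and its baseline may not be a rested value

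*Protocol article*

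**What the plan says.** Section 2.3 sets out the structure: "Each participant will take part in two phases of the experiment including familiarization and data collection". Section 2.3.1 then says that all subjects will "undergo a familiarization session, about 1–2 h before data collection". It puts two things in this phase.

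- **Load selection:** "The weight plates used in the trunk muscles fatigue protocol for each participant will be chosen during the familiarization phase", by the rule "The heaviest weight that participants can perform each exercise 20 times in 40 s in the correct form will be used".
- **The pre-test restriction:** "During this phase, subjects will be asked to eat their normal meal while avoiding strenuous exercise". The full restriction is "avoiding strenuous exercise and performance-enhancing energy drinks for the 48 h prior to data collection sessions".

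Section 2.3.3 (Fatigue protocol) describes load selection again but times it differently: "The selection of weight plates for each subject will be performed on a separate day before testing". The rule is the same: "The heaviest weight with which subjects can perform each exercise 20 times in 40 s in the correct form will be used".

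Section 2.3.2 lists the pre-fatigue assessment as the baseline. The Abstract gives one week of rest between the two recovery conditions.

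**The concern.** The two sections describe one procedure, with one selection rule and two timings. Staff working from 2.3.1 would choose the loads on the test day, and staff working from 2.3.3 would not.

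The choice affects the measurements in two ways. A 48 h restriction can be obeyed only by someone told of it at least 48 h ahead, and the 2.3.1 timing does not allow that for the first session. Load selection is also trunk work at the heaviest load a participant can manage for 20 repetitions, which is the working set of the fatigue protocol itself. Done an hour or two before the baseline, it may mean that the value labelled pre-fatigue is not taken at rest.

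The baseline is the reference point for a study of recovery from fatigue. Section 2.4 compares all assessment times within each group, baseline included, and also compares the groups from baseline to the final follow-up.

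**Working it through.** The point turns on timing and consistency, so no power or sample-size calculation applies.

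**1. Is it the same procedure?** Both sections concern the weight plates for the fatigue protocol, and both use the heaviest load allowing 20 repetitions in 40 s with correct form. One says the familiarization phase, whose only stated session is about 1–2 h before data collection. The other says a separate day. A session 1–2 h beforehand is not naturally a separate day, so the two timings conflict.

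**2. Lead time for the 48 h instruction, on the 2.3.1 timing.**
- Required lead: 48 h (2.3.1).
- Available lead before session 1: 1 to 2 h (2.3.1).
- Shortfall: 48 − 2 = 46 h to 48 − 1 = 47 h.
- Available lead before session 2: at least 7 × 24 = 168 h (one week, Abstract), which exceeds 48 h.

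The problem is therefore confined to session 1, for all participants handled this way.

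**3. How much work load selection involves.** As a check on the inputs, the stated protocol length reproduces: 4 cycles × 8 exercises = 32 bouts, and 32 × (40 s + 20 s) = 1,920 s = 32 min, as 2.3.3 states. Section 2.3.3 names three exercises done with a weight plate (the fourth, fifth and sixth in its list). The least that load selection can involve is one successful set of each:
- 3 × 20 = 60 repetitions;
- 3 × 40 s = 120 s = 2 min of work;
- 3 / 32 = 9.4% of the protocol's bouts.

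Finding the heaviest load would normally take more than one attempt, but the number of attempts is not stated. These figures count work done. They do not measure fatigue remaining.

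**4. Can a bias be computed?** No. The article gives no recovery curve for the trunk muscles, so what is left 1–2 h after such sets is unknown. The direction is also open. Residual fatigue could shift the baseline towards the post-fatigue value. Section 2.3.2.2.2, however, specifies no warm-up before the spinal mobility examination, so for range of motion earlier activity might act as a warm-up instead.

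**5. Which analyses use the baseline?** The within-group comparisons across times and the between-group analysis from baseline to final follow-up do (2.4). The non-parametric between-group comparison at each post-recovery assessment does not.

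**The case against.** The strongest reply is that this is an editorial slip. Section 2.3.3 gives an explicit, workable arrangement. Section 2.3.1 uses its terms loosely (a second phase appears under the Familiarization heading), so the familiarization phase might extend beyond the 1–2 h session. There are also contacts before data collection: screening with two questionnaires (2.2.1), consent, and a health questionnaire completed before the study (2.3.1.1). The flow diagram is not visible and might show the visit schedule. Participants are screened as sedentary and may meet the restriction without being told, and strenuous is not defined.

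Much of this stands. A longer familiarization phase is possible, lateness does not prove non-compliance, and whether load finding breaches the restriction depends on an undefined word. But the text shown does not place the 48 h instruction or load selection at any of those earlier questionnaire or consent contacts, and a figure could not remove the conflict between the two sentences.

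Three stronger readings are tempting, and the document supports none of them.

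- **Understated fatigue effect.** A reader might infer that the fatigue effect will be understated and recovery will look too complete. That needs a residual effect of known sign at 1–2 h, which the document does not give.
- **Bias in the active-versus-passive comparison.** That would need an effect falling unequally on the two modalities, which has not been shown. Changes from post-fatigue to post-recovery do not involve the baseline at all.
- **The 2.3.3 timing as a further error.** A separate day might be the day before, but that is an assumption. The exact gap is detail an article may leave to the full protocol.

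**Conclusion.** The conflict is real and should be resolved before the procedure is run or reported. It goes beyond wording, because following 2.3.1 as written defeats the plan's own restriction. The instruction is 46–47 h late for session 1, and sets at the heaviest 20-repetition load precede the session-1 baseline on the same day. Session 2 has adequate notice.

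This conclusion is conditional on the 2.3.1 timing being the one used. It also takes the phase in which the restriction is given to be the familiarization phase, which is the natural reading but not a certain one. Under those conditions the session-1 baseline may not be a rested value. How far it would be distorted, and in which direction, is unknown. No effect on the comparison between recovery modalities is claimed.

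**What to change.** Correct section 2.3.1 to agree with 2.3.3. Move load selection and the 48 h instruction to the separate visit, and schedule that visit at least 48 h before the first data-collection session so that the plan's own restriction is met. Keep the session 1–2 h before data collection for explanation and practice only, with no loaded trunk exercise.

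The cost is a wording change and the scheduling of a visit that 2.3.3 already foresees. No outcome, analysis or sample size changes.

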##### 2.3.1.1 Health and safety considerations

Participants will complete a “health and medical questionnaire” before the study and will be closely monitored by professionals to minimize injury risk. Participants will stop exercises if experience pain or discomfort. Adverse events will be documented and addressed, with modifications to the protocol if necessary.

#### 2.3.2 Data collection

Data from all participants will be collected under three conditions:1. Pre-fatigue assessment (at baseline),2. Post-fatigue assessment (immediately after fatigue protocol),3. Post-recovery modalities assessment (immediately, and 15-min after cessation of active and passive modality, respectively).

Assessing the effects of the intervention at the 15-min follow-up can provide insight into the potential duration of these effects.

All participants will be tested at the same time of day by the same examiners.

The study will involve gathering individual demographic information and outcome data. The study team will enter the questionnaire data into a database and verify its accuracy before using it. All information and outcome data will be kept on password-protected computers that only the authorized members of the study team will be able to access. Data management will outline the procedures for gathering, recording, storing, and archiving data.

##### 2.3.2.1 Primary outcomes for screening

###### 2.3.2.1.1 International physical activity questionnaire

Potential participants will be screened for the study using the International Physical Activity Questionnaire [IPAQ] to recognize those who are sedentary. The IPAQ is a formal self-report tool used to measure physical activity in one’s normal daily routine (Mehta et al., 2018). This questionnaire is available in two versions, long and short (Demircioğlu et al., 2021). The IPAQ short form (IPAQ-SF) is used to screen physical activity levels in the population at large, while the IPAQ long form (IPAQ-LF) is used in research studies or clinical settings to assess physical activity levels (Mehta et al., 2018). In both versions of the questionnaire, the common objective is to assess the amount and intensity of physical activity an individual participates in per week (Mehta et al., 2018). Each version considers four domains: leisure-time physical activity work-related activities, domestic and gardening activities, and transport-related activities. The long interview administered version of the IPAQ, which contains 27 items in the four domains, will be used in the present study (Mehta et al., 2018). Using the long form, it will be possible to calculate domain-specific scores, activity-specific scores, and continuous scores. The continuous scores, expressed in metabolic equivalent minutes (MET), will be a measure of physical activity. According to these scores subjects will be categorized as engaging in low-, moderate-, or high-level physical activity (Mehta et al., 2018).

###### 2.3.2.1.2 Acute low back pain screening questionnaire

The Acute Low Back Pain Screening Questionnaire (ALBPSQ) identifies those who are at risk of developing non-specific low back pain. The questionnaire has been endorsed by guidelines from the New Zealand work health authority (Hanna et al., 2019). The level of back pain will be calculated based on the duration and intensity of the pain. A Likert rating scale from 0 (no pain) to 5 (pain as bad as it can get) will be used to assess perceived beliefs about the psychological impact of pain on the participant. Ratings on the scored items will be subsequently summed to determine a total score and domain sum score. A higher rating indicates a higher level of risk.

##### 2.3.2.2 Secondary outcomes for intervention evaluation

###### 2.3.2.2.1 Assessment of the trunk muscle fatigue

The Delsys Trigno™ wireless EMG system, will be used to record electromyography signals from the trunk and hamstring muscles. These muscles will be the lumbar multifidus at the L5 level, and erector spinae muscles at the L1 level and hamstring muscles. Prior to electrode placement, the skin will be prepared by abrasion and cleaning with alcohol.

For the Multifidus Muscles⁃ Electrode placement: on the line connecting the caudal tip of the posterior superior iliac spine (SIPS) to the space between L1 and L2, at the level of the spinous process of L5, 2–3 cm from the medial line,⁃ Inter-electrode distance: 25 mm,⁃ Clinical test: maximum isometric strength of the back extensor muscles.

For the Longissimus Muscles: erector spinae⁃ Electrode placement: two fingers apart in a lateral direction from the spinous process L1,⁃ Inter-electrode distance: 25 mm,⁃ Clinical test: maximum isometric strength of the back extensor muscles.

For the Hamstring Muscles: medial hamstring⁃ Electrode placement: The medial hamstring on both lower extremities: the electrode for the medial hamstring will be placed midway between the ischial tuberosity and the medial epicondyle of the tibia,⁃ Clinical test: maximum isometric strength of the hamstring muscles.

The raw sEMG signals will be recorded at a sampling frequency of 2,000 Hz. Butterworth band-pass filters with a passband of 20 Hz and a stopband of 450 Hz will be applied to remove signals that will not be due to muscle activity. The features of muscle fatigue by EMG are amplitude increase and transformation from a high-frequency spectrum to a low-frequency spectrum. It is assumed that fatigue and recovery are mutually exclusive. Therefore, decrease amplitude and transformation from a low-frequency spectrum to a high-frequency spectrum are features of muscle recovery by EMG. In the present study, the mean amplitude (root mean square, RMS) and the frequency features (mean power frequency, MPF, and median frequency MDF) of the sEMG signals will be used to evaluate muscle fatigue and recovery. To accomplish this, the raw EMG signal will be processed with a fast Fourier transformation to determine the mentioned variables. The fast Fourier transform is a mathematical technique used to transform a time-domain signal into its frequency-domain representation (Mateo and Talavera, 2018).

###### 2.3.2.2.2 Assessment of the spinal mobility

Intersegmental mobility, overall and regional spinal range of motion will be measured in the sagittal plane in the standing position using a Spinal Mouse device (Csuhai et al., 2020). It is a wireless electronic, and non-invasive skin-surface tool for computer-assisted imaging and radiation-free examination (Post and Leferink, 2004). The Spinal Mouse’s reliability and validity have been established in populations that were healthy and symptomatic, including back pain (Topalidou et al., 2014). Before starting the examination, every subject will be registered in Spinal Mouse software with gender, age and randomly allocated study codes. Subjects will be asked to take three different standing positions: relaxed but erect (not corrected), maximal flexion and maximal extension of the spine. After undressing the upper body, spinous processes will be palpated, and C7 and S3 will be marked with a body-marker. Spinal Mouse will run paravertebrally along the spinous processes of marked segments. It makes the system capable of recording the contour of skin above the vertebral bodies in the sagittal plane. Positions include:1. Neutral in standing: Subject will be asked to maintain a relaxed position with the feet shoulder width apart, with straight knees and arms by the side, looking and facing straight horizontally towards the wall.2. Maximal flexion in standing: Subject will be asked to flex the trunk with straight knees as far as possible with slow motion from segment to segment, aiming to touch the ground with fingertips.3. Maximal extension in standing: Subject will be asked to cross arms in front of the chest and extend the trunk as far as possible, keeping the knees straight, without extension of the cervical spine.

No warm-up will be performed before the examination and each test will be done once (Post and Leferink, 2004). The mobility values of the segments, including range of flexion from upright (U-F), range of extension from upright (U-E) and total range from extension to flexion (E-F), will be measured (Csuhai et al., 2020).

###### 2.3.3.2.3 Assessment of the postural stability

Participants will be asked to stand barefoot on a force plate with their arms relaxed comfortably at their sides. They will be instructed to stand in an upright position with their feet abducted at 10° and their heels separated mediolaterally by a distance of 6 cm. A series of trials will be conducted in a randomized order under varied conditions: tandem stance on a force plate with eyes open, tandem stance on a force plate with eyes closed, tandem stance on a foam mat (Airex Balance Pad) placed on the force plate with eyes open, tandem stance on a foam mat (Airex Balance Pad) placed on the force plate with eyes closed (Zemková et al., 2016). Subjects will perform one set of 30s under each condition. Short rest periods break will be allowed after every two trials (Zemková et al., 2021c).

Postural stability will be assessed using a FiTRO Sway Check (FiTRONiC, Bratislava, Slovakia). The system measures the actual force in the corners of the force plate and calculates an instant position of the CoP (sampling rate: 100Hz, 12-bit AD signal conversion, resolution of the CoP position: less than 0.1mm, measuring range: 0–1,000/s, non-linearity: ±0.02%FS, combined error: 0.03%, sensitivity: 2 mV/V ± 0.25%, overload capacity: 150%/sensor). FiTRO Sway Check has been shown to have good to excellent reliability of CoP variables, according to a recent study by Zemkova et al. (2021) (Zemková et al., 2021c). The Romberg quotient (eyes closed/eyes open (EC/EO) sway ratio) will also be calculated. Under unstable conditions, variables of postural stability will be registered by using the FiTRO Sway Check (FiTRONiC, Bratislava, Slovakia). The device consists of a square platform supported by four springs with an elasticity coefficient of 40N/mm. Shifting the CoP in the horizontal plane leads to changes of body weight distribution to the four corners of the platform. Force acting in each corner is calculated as a product of the coefficient of elasticity of the spring used and vertical distance measured by means of a fine sensor. The analogue signals are AD-converted and sampled by computer at the rate of 100Hz. Calculations of instant CoP position is based on force distribution to the four corners of the platform. Basic parameters of postural stability (i.e., mean CoP velocity and mean CoP displacements in medio-lateral and anterior-posterior directions) will be analyzed (Zemková et al., 2021c).

#### 2.3.3 Fatigue protocol

The modified Abt protocol will be used in order to induce fatigue of trunk muscles (Abt et al., 2007). The protocol lasts 32 min and consists of four consecutive cycles of eight exercises. Each set consists of exercises in the following order:1) trunk rotation with a medicine ball in a sitting position, 2) prone static torso extension with a medicine ball, 3) lower torso rotation with a medicine ball in a supine position, 4) sit-ups on the incline bench with a weight plate, 5) lateral side binding with a weight plate, 6) lumbar extension rotation with weighted plate, 7) trunk rotation with weighted pulley resistance in standing position, and 8) supine isometric bridge hold. The selection of weight plates for each subject will be performed on a separate day before testing. The heaviest weight with which subjects can perform each exercise 20 times in 40 s in the correct form will be used. Prior to trunk muscle fatigue protocol, a 10- minutes warm-up will be performed including 5 min of *insitu* warming, and 5 min of aerobic stretching, with an emphasis on the hamstring and trunk muscles. Then fatigue protocol will be started. Subjects will perform 20 repetitions of each exercise in 40 s (each repetition in 2 seconds). A pause of 20 s will be between each exercise. The fatigue protocol will be terminated in two ways: 1) when subjects will be no longer able to continue the fourth set of exercises (the last set) with the correct form, and 2) when the subjects will be unable to perform each repetition in 2 seconds in the last set exercises. To ensure occurrence of fatigue, subjects will be rated on their perceived exertion at the end of each phase of the protocol using the 15-point Borg scale (rank 6–20) (Borg, 1970). The point of six represents the absence of fatigue and point of 17–20 indicates failure to perform exercises. If the subjects in the end of fourth round report number 17 or higher, it means the end of the fatigue protocol. If they will report fewer points, they should perform another round until they report the point 17 (Askari and Esmaeili, 2021).

